**3.4** **Safety: T cell vaccination subcutaneous administration to multiple sclerosis patients.**

Immunization with irradiated autologous myelin specific cells using similar protocol (19) has been shown safe without any significant side effects. Results obtained so far demonstrated that TCV was not associated with serious adverse events as evidenced by standard toxicological tests. Three injections of the suggested amount of irradiated autologous T-cells did not affect the T-cell repertoire and the reactivity against other antigens. Mild side effects previously reported include skin reaction at the injection site, especially after the third immunization; this reflects a local delayed T-cell mediated hypersensitivity response. The possibility of infections due to transmission of infectious agents from the cultured cells is, according to previous reports, very low if at all (19).

**3.5 Rational of conducting the study.**

Rational for conducting the study: the purpose of this study is to develop a T-cell vaccination protocol using autoantigen-specific T-cell lines, and to test its efficacy to inhibit the development of neurological disability in patients with Multiple Sclerosis (MS). Multiple Sclerosis is an autoimmune inflammatory disease mediated by autoreactive T-lymphocytes which attack the proteins (MBP, PLP, MOG, MAG) of myelin sheath, inducing therefore multifocal demyelination and subsequent multi-level central nervous system dysfunction. It is the main cause of chronic (and permanent) neurological disability in the young population (mean age of disease onset~32, mean disease duration~20-30 years). In Israel, there are 3,000-5,000 patients today. The conventional treatments for MS are focused on down-regulation of the autoimmune, myelin-reactive lymphocytes in an attempt to inhibit the continuous (usually relapsing and remitting) demyelination. Corticosteroids and various immunosuppressants (cytotoxic/cytostatic drugs –chemotherapy- and modalities) and immunomodulating (interferons) drugs have been used the last decades for the management of this disease, but unfortunately with limited success and cumulative toxic side effects due to their lack of specificity in their action on immune cells (normal cells are, equally to the autoimmune ones, destroyed by chemotherapy). T-cell vaccination is a new approach which has the advantage of high specificity and low potential toxicity. Apart from its potential therapeutic value, this procedure may provide a new insight to the immunopathogenesis of MS.

1. **Study Objectives**

To assess the efficacy, safety of vaccination with 10-50 millionsdead-autologous anti-PLP, anti-MBP and anti-MOG peptides autoreactive T-cells injected subcutaneous four times (at day zero and after 30, 90 and 180 days) to Relapsing Progressive MS patients during 12 month period.

**4.1 Primary Efficacy Endpoint**

Efficacy will be measured by using an "intention to treat" analysis. The establishment of Primary Efficacy Endpointwill be based on the ∆ EDSS will be calculated for each patient by subtracting the beginning and end point EDSS scores. Mean EDSS scores for the two groups (treatment vs. placebo) will be calculated.

The Area Under the Curve (AUC) of the Change from Baseline in EDSS Score: The AUC of the individual changes from baseline in the EDSS score will be calculated suing the trapazoidal rule. The actual dates on which measurements were obtained will be used for this calculation. All EDSS measurements, including those made while the patient experiences a relapse, will be included. This measure will be divided by time on trial to account for variable trial’s exposure periods.

This measure will be tested using baseline-adjusted analysis of covariance. Statistical methods will be used to compare the adjusted means of the two test contrasts incorporating terms from treatment. Baseline EDSS scores will be included in the model as a covariate. The Total Number of Relapses and Relapses Treated with Steroids: Any relapse observed and/or those treated with steroids will be counted and included in this analysis. Statistical analysis will employ the same procedures as described from the primary end-point.

**Primary Safety Endpoint**

The primary safety endpoint for this study are the safety profile of adverse experiences, the tolerability will be based on the number of patients completing the study.

- 1. **Secondary Efficacy Endpoints:**

Changes from the baseline of clinical parameter; 10 meter walking test, 9-Hole-peg Test, PASAT cognition test and the Ambulatory Index (AI).

The total number of T1-Gd enhancing lesions (in MRI) and of T1 hypo dance black holes.

The volume of T2 lesions: (in MRI) and the degree of brain atrophy i.e. BPF (brain parenchymal factor) width corpus colossus and of lateral ventrical).

**Secondary Safety Endpoints:**

Safety profile of: 1. Clinical laboratory parameters

1. Vital sign
2. ECG
   1. **Tertiary Outcome Measures:**

Proportion of relapse free patients

Time to first relapse.

Proportion of second relapse free patients

Time to second relapse.

Brain atrophy (whole brain).

Number and proportion of activated lymphocytes.

Number and proportion of anti-myelin reactive lymphocytes in the peripheral blood and IgG antibody levels in the cerebrospinal fluid

**5. STUDY DESIGN**

**5.1 Overview**

This is a one center, randomized, double-blind, placebo-controlled study comparing 10-50x106 dead cell vaccine versus placebo in relapsing progressive multiple sclerosis patients (in which severe deterioration in the functional status of at least, one degree in the EDSS scale was observed during the last year) for duration of 12 month (active treatment continuation optional).

All patients will undergo MRI at baseline and at termination.

Visit will be conducted at screening (visit 1), randomization (at visit 8) and then one, three, six, eight, ten, and twelve month after visit 8 (the baseline). The vaccination treatment will be administrated in visit 8, 9, 10 and 11. The patients will be further monitored in visits 12 till 14.

Unscheduled visits may be conducted whenever required, such as adverse events and exacerbations.

The patients will be recruited from the Hadassah MS Clinic.The medical staff will include the treating nurse, the treating physician (The one who will perform the regular follow up registration of Adverse Events AE* and evaluation of relapses) and the examining neurologist (the one who will perform the neurological evaluation).

**5.2 Patients Assignment and Treatment Groups**

Patients who meet all eligibility criteria will be randomly assigned in 1:2 ratio to one of the following groups:

- Group A: 10-50x106 dead T-cells vaccine (20 patients)
- Group B: Placebo (sterile normal saline) (10 patients)

**5.3 Study Plan**

After obtaining informed consent, patients will be evaluated for inclusion into the study. Vaccine will be prepared form PLP, MOG, MBP peptide specific autologous T–cells for the appropriate patients. Group A will be treated with the T cell vaccine and group B will be subjected to the placebo. The T-cell vaccine prepared for group B will be properly stored (will be frozen) and will be used after the study is concluded if study shows a beneficial affect for the patients. The effects of immunotherapy will be evaluated on the basis of the clinical, neuroradiological (MRI), and immunological assessments (optional) carried out at inclusion, every three months following the treatment and at the end of the 12-month period of the trial (one year after the first injection).

**5.3.1 Study Location**

The study will be conducted at:

The HBRC (Human Biology Research Center) in the Nuclear Medicine and Medical Biophysics Department.

Vaccine preparation will be performed at The GMP Clean rooms in the Vector Production Facility.

The Neurological Department Hadassah

All are located at Hadassah Hebrew University Hospital, Jerusalem, Israel.

the GMP (good manufacturing practice) clean rooms of the Vector Production Facility Center both at Hadassah Hospital, Jerusalem.

Screening Failure

**Eligible**

**Base line Evaluation***

Clinical Evaluation

MRI Scanning

Laboratory Evaluation

**Not Eligible**

**Screening Success**

**Randomization**

**Placebo**

10 Patients

**T cell vaccination**

(10-50x106dead cells)

20 Patients

**On study evaluation**

**Final Evaluation***

Clinical Evaluation

MRI Scanning

Laboratory Evaluation

**Open labels**

Result analysis

Conclusion

T-cell vaccination of the placebo group-optional

***** As specified in the next table “study task flow sheet”

**Screening Evaluation***

Eligibility Criteria

Signing on informed consent forms

Medical history

Historical and Concomitant Medications

Physical Examination

Neurological Exam and test

Serum β HCG

Inclusion criteria review process

Screening and production of MOG, MBP peptides-responding-T cell vaccine

**Study Activities Flow Chart**

**STUDY TASK FLOW SHEET**

| Procedures | Screening | TCV Processing | Baseline | On Study Evaluation | | | | | |
| --- | --- | --- | --- | --- | --- | --- | --- | --- | --- |
|  | | | TC Injections | | | |  | | |
| *Visits* | 1 | 2-7* | 8 | 9 | 10 | 11 | 12 | 13 | 14 |
| *Months* | *-3* | -2 | 0 | 1 | 3 | 6 | 8 | 10 | 12 |
| Informed Consent | X |  |  |  |  |  |  |  |  |
| Eligibility Criteria | X |  |  |  |  |  |  |  |  |
| Medical History | X |  |  |  |  |  |  |  |  |
| Historical and  Concomitant Medications | X |  | X | X | X | X | X | X | X |
| Physical Examination | X |  |  |  |  |  |  |  | X |
| Neurological Exam and test | X |  | X | X | X | X | X | X | X |
| Laboratory Evaluation/Immunology |  |  | X |  |  | X |  |  | X |
| Serum β HCG | X |  |  |  |  |  |  |  | X |
| MRI-cerebral |  |  | X |  |  |  |  |  | X |
| Randomization |  |  | X |  |  |  |  |  |  |
| TCV |  |  | X | X | X | X |  |  |  |
| Adverse Experiences |  |  | X | X | X | X | X | X | X |

* Weekly visits for blood withdrawals for TCV preparation.

Preparation of T-cell Vaccination

Activity Flow Chart

**Days + visits**

**Protocol**

**PBMC Isolation-**

Ficoll Paque

PLP/MBP/MOG peptide activation

20 µg/ml

(

2x 12 million cells)

**Blood**

-

50 ml heparinized

patient's blood

**Protocol**

day 0

**visit 2**

**Assays**

**Reactivation I-**

7000 rad Irradiated

autologous APC pulsed with PLP,

MBP or MOG peptides

5-20 U/ml rIL-2 (BM)

**Irradiation**

6000 rad

**Preparation for injection**

1

0-50 million cells in 1-3 ml saline

**QC tests**

**:**

2-5 days prior to injection

Microbiology: THIO,TSB

blood agar

micoplasma, endotoxin

viability >70%

Facs analysis

**T-cell Vaccination Protocol for Multiple Sclerosis Patients**

Clinical trial- Phase I/II

QC- Blood Microbiology

**Freeze**

-

10 million/vial

3-15 aliquots

QC- endotoxin

LAL test for PLP/MBP/MOG

peptides, IL-2 and media

additives

day 7

**visit 3**

day 14

**visit 4**

**Reactivation II-IV**

day 17-31

**visits 5-7**

**Subcutaneous Injection**

**Screening-**

3

H

thymidine uptake 3 days assay

expansion of PLP/MBP/MOG lines with

selected peptides

to validate

**PLP, MBP**

**MOG peptide specific T-cell**

**line**

day 35

**visit 8**

Facs analysis

day 0

**visit 1**

**Validation of MBP, PLP**

**MOG responsiveness**

(50 ml patient's blood)

Proliferation assay to PLP,

MBPand MOG peptides

and recall antigens

**Screening-**

3

H

thymidine uptake 3 days assay

expansion of PLP/MBP/MOG positive

wells with

selected peptides

**PLP MBP MOG specificT-cell line**

day 31

visit 7

**visits 9-11**

**3 injections of frozen cells**

**6. STUDY POPULATION**

**6.1 Number of patients**

Thirty Relapsing-Progressive Multiple Sclerosis (R-P MS) patients will be randomized into two groups. The first group will include 10 patients (placebo) and second 20 patients (TCV treated). Drop-out will be replaced. The patients will be recruited from the Hadassah MS clinic.

**6.2 Patient Selection**

Prior to or at the screening visit, all patients will sign and date an Inform Consent Form approved by the Hadassah Helsinki Ethic board and the Israeli Health Ministry Office. Screening will be performed according to the study task flow sheet.

**6.2.1 Inclusion Criteria**

To be eligible for inclusion into the study, each patient must fulfill the following criteria:

1. Clinically definite MS of the relapsing-progressive type (RPMS) according to Poser’s criteria (16).

2. Age; 18-60 years old, inclusive.

3. EDSS: 3.0 to 6.5, inclusive

4. Disease duration: above one year.

5. Evidence of disease progression of 1 degree in the EDSS scale, or at least two severe relapses (needed hospitalization and treatment) during the last year prior to inclusion.

6. MRI of the brain with at least 5 lesions in the white matter (T2 imaging).

7.Failure of other existing treatments according to the guidelines of the Israeli Ministry of Health.

8. All patients will sign the written informed consent form.

9. Males and female (birth control, where appropriate)

10. Patients that their T cells will respond, and be activated by the myelin-derived peptides and a specific T-cell-vaccine can be produce for them.

**6.2.1 Exclusion Criteria**

Patients are to be excluded from the study if any of the following criteria is being fulfilled:

1. Patients with other systemic active disease.

2. Patients who were treated with immunosuppressive drugs/modalities during the 3-6 months (depending on the cytotoxicity of the medication used) prior to the inclusion.

3. Pregnancy; Pregnant women or women without any efficacious contraception (oral contraception, or intra-uterine device).

4. Patients with an additional MS-unrelated autoimmune condition or significant allergy.

5. Patients who cannot fully understand the treatment protocol or are unable to sign the informed consent.

6. Patients who have previously received cellular immunotherapy.

7. Patients for whom the clinician thinks that a follow-up period of at least 12 months will not be possible.

8. Patients who are participating in other experimental protocols.

**7. Assessments**

# 7.1 Clinically Definite MS

A standardized questionnaire will be used to record MS history for each patient. This information will be used by the investigator to determine if the patient meets the inclusion criteria with respect to the existence of history consistent with clinically definite MS as defined by Poser *et al.* (Ann. Neurol. 1983):

- Two attacks and clinical evidence of two separate lesions
- Two attacks; clinical evidence of one lesion and para-clinical evidence of another separate lesion.
  1. **Neurological Evaluations**

Functional Systems status (FS), Ambulation Index (AI), 10 Meter Walking Test, 9-Hole-peg test PASAT cognition test. and Expanded Disability Status Scale (EDSS) will be performed, scores will be assessed based on standardized neurological examination.

**7.3. Relapse Evaluation**

# 7.3.1 Relapse Evaluation Procedures

- Patients will be instructed to telephone their study site immediately should any symptoms suggestive of a relapse appear.
- The patient has to be examined within 7 days of telephone contact as follows:
- The Treating Physician (see Section 15.1.2) will evaluate the patient once any symptom suggestive of a relapse occurs.
- In case of a suggestive relapse during scheduled or unscheduled visit, the Treating Physician will refer the patient to the Examining Physician (see Section 15.1.3).

# 7.3.2 Relapse Definition

A relapse will be defined as the appearance of one or more new neurological abnormalities or the reappearance of one or more previously observed neurological abnormalities. This change in clinical state must last at least 48 hours, and be immediately preceded by a relatively stable or improving neurological state of at least 30 days.

An event is counted as a relapse only when the patient’s symptoms are accompanied by observed objective neurological changes, consistent with an increase of at least 0.5 in the EDSS scores or one grade in the score of two or moreof the seven Functional Systems (FS) or two grades in the score of one of the FS as compared to the previous evaluation.

The patient must not be undergoing any acute metabolic changes such as fever or other medical abnormality. A change in bowel/gladder function or in cognitive function must not be entirely responsible for the changes in EDSS or FS scores.

# 7.3.2.1 Patient Evaluation by the Examining Physician

A complete neurological assessment will be performed at each scheduled visit, including: FS, AI, Kurzke EDSS, and 10 Meter Walking Test, 9-Hole-peg test PASAT cognition test.

# 7.3.2.2 Relapse Determination by the Treating Physician

The decision as to whether the neurological change is considered a relapse will be made by the Treating Physician, based on EDSS/FS scores assess bye the Examining Physician.

Follow-up visits to monitor the course of the relapse will be made at the Treating Physician’s discretion, in addition to the assessment at the next scheduled visit, but the neurological assessments will be performed by the Examining Physician.

In case of an ongoing or just started relapse at study termination visit, patients will be followed until the end of the relapse, wherever possible.

**7.3.2.3 Relapse Treatment**

The Treating Physician will make the decision whether or not cortico-steroids should be administered for the treatment of the relapse. A fixed dose of 1g/day of (Methyl Prednisolone Solumedrol) for 5 consecutive days, is the treatment suggested in this protocol.

**7.4 MRI Evaluations**

- All patients will undergo MRI at baseline and at study completion:
  - Total number of T1-Gd enhancing lesions
  - Volume of T1-Gd enhancing lesions
  - Volume of T2 lesions
  - Total number of New T2 lesions
  - Brain atrophy
  - Total number and volume of hypo-intense lesions in T1 scans

**Steroid treatment for relapse will not affect the time schedule of MRI scans.**

All MRI data will be interpreted in a blinded fashion by the MRI Analysis Center (MRI-AC). MIR can be preformed up to 72 hours (3 days) prior to baseline, and within 10 days after the end of the study.

**7.5 Adverse Experiences**

All adverse experiences will be reported and documented as detailed in Section 11 of this Protocol. The relation of adverse experiences to the treatment will be determined according to WHO guidelines.

**7.6. Laboratory Evaluations**

All laboratory testing will be performed in our laboratories at the Hadassah University Hospital in Jerusalem.

-Serum chemistry

- - Glucose
  - Creatinine
  - Calcium
  - Total Bilirubin
  - Urea
  - AST (SGOT)
  - ALT (SGPT)
  - Cholesterol
  - Total protein
  - Albumin
  - Alkaline Phosphates
  - Phosphorous
  - Sodium
  - Potassium

-Hematology

- - Hemoglobin
  - Hematocrit
  - Red Blood Cells (RBC)
  - White Blood Cells + differential count
  - Platelets

-Urinalysis

- - Protein
  - Glucose
  - PH
  - Blood

-Serum β HCG for female patients (at screening visit and termination).

- Immunological (optional) follow up: Immunological follow-up of the patients will include the detection of:

- Frequency of the **specific auto-reactive** T-cells injectedone year from the last injection.
- Frequency of activated lymphocytes to recall antigens one year from the last injection.
- Frequency of **anti-myelin reactive** **lymphocytes** (**anti-clonotypic)** in the peripheral blood.
- Anti-idiotypic antibody levels in the peripheral blood.

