**9.1 Pre-Enrollment (Screening) Evaluation (Visit 1)**

The patient will be assessed for eligibility criteria by the Treating Physician and neurologically examined by the Examining Physician. Patient’s pre-enrollment must occur within 60 days prior to randomization and the first treatment. Screening evaluation must assure that all inclusion and exclusion criteria have been met.

During the screening visit, the patient must be thoroughly informed about all aspects of the study, including scheduled study visits and activities, and must sign the informed consent.

The following procedures will then be performed:

- Physical examination;
- Vital signs;
- Medical history;
- Historical/concomitant medications;
- History of multiple sclerosis;’
- Neurological evaluation;
- ECG and Chest X-rays;
- Clinical laboratory studies, including:
  - Serum pregnancy test (β HCG) for women;
  - Urinalyses;
  - Hematology;
  - Serum chemistry;
  - Serum samples and lymphocytes for immunological studies.

- Evidence of relapse;

- Inclusion/exclusion criteria;

- - 1. **Screening for patients that their T-cells react to the specific peptide**

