**9.3 Month 0 Baseline Evaluation – First Day of Treatment (Visit 8)**

Prior to randomization, the following will be assessed:

- Changes in medical condition since screening;
- Concomitant medication changed since screening;
- Physical changes since screening;
- Clinical laboratory tests; Routine hematology, blood chemistry, and urinalyses
- Neurological exams including FS, AI, EDSS, 10 Meter Walking Test, 9-Hole-peg test PASAT cognition test.
- Evidence of relapse;
- MRI
- Inclusion/Exclusion criteria confirmation;
- Pre-dose vital signs.

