**9.4 Treatment Period (visits 8-11).**

The treatment period will include 4 visits (Visits 8-11), on day 1 (first injection) and months 1, 3, and 6. Following the first injection of the TCV (visit 8) there will be additional 3 boosts of the TCV that will be schedule to month 1, 3, 6 (visits 9, 10, 11). Two subcutaneous (S.C.) injections (1.5-3 ml of dead cell preparation) will be prepared each time: one for each arm and each will contain a mixture of lines specific for one protein. For the schedule of injections and visits, see the following table:

| **Visit** | **Injection #** | **Day #** | **# of Fixed Cells** |
| --- | --- | --- | --- |
| **8** | **1** | **1** | **10-50 x 106** |
| **9** | **2** | **30** | **10-50 x 106** |
| **10** | **3** | **90** | **10-50 x 106** |
| **11** | **4** | **180** | **10-50 x 106** |

In addition the patients will be examined.

- Neurological assessment will be performed at months 1, 3, and 6. The Examining Physician **should not** refer to previous neurological assessments carried out on the patient, prior to the completion of the visit’s neurological assessment;
- Routine hematology, blood chemistry, ad urinalyses will be performed at months 6 (visit 11).
- Documentation and follow-up of each exacerbation will be conducted through the study period.
- Adverse events will be followed carefully at each visit by the Treating Neurologist;

The injection site on the patients arm will be covered by bandage before the examination. Thus, the evolution will not be biased by differences between the placebo and the TCV at injection site.

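### Pregnancy bars entry and ends participation, yet no pregnancy test is scheduled between screening and month 12, so all four injections rest on a screening result at least 35 days old

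*Protocol*

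**What the plan says.** Section 7.6 (Laboratory Evaluations) places the test at two points: "Serum β HCG for female patients (at screening visit and termination"). In the study task flow sheet the row "Serum β HCG" is marked at visit 1 and visit 14 and blank at every visit between. Section 9.1 carries the visit 1 test as "Serum pregnancy test (β HCG) for women" and says that "pre-enrollment must occur within 60 days prior to randomization and the first treatment"; the flow sheet puts visit 1 at month -3.

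The pregnancy rules are these:

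- Exclusion criterion 3 (section 6.2.1, Exclusion Criteria): "Pregnancy; Pregnant women or women without any efficacious contraception (oral contraception, or intra-uterine device").
- Section 9.3, to be done at visit 8 before randomization: "Inclusion/Exclusion criteria confirmation".
- Section 9.7.2.1 lists pregnancy among the reasons for premature discontinuation.

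The laboratory work between the two tests is, at visit 8, "Clinical laboratory tests; Routine hematology, blood chemistry, and urinalyses", and in the treatment period, "Routine hematology, blood chemistry, ad urinalyses will be performed at months 6 (visit 11"). The urinalysis panel in section 7.6 covers protein, glucose, pH and blood.

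**The concern.** The protocol treats pregnancy as decisive at entry and throughout dosing, but gives the site no current test result on which to act at either stage. A woman who conceives after screening, during the weeks of vaccine preparation, can be passed as eligible at visit 8 on an out-of-date negative result. She would then have the baseline gadolinium scan and receive injection 1. A conception during months 0 to 6 can likewise go unrecognised through later injections, although it should lead to discontinuation. The termination test at month 12 comes six months after the last injection, too late to prevent any exposure.

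What is at stake is participant safety and the site's ability to apply the protocol's own rule. The treatment comparison is not at stake.

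**Working it through.** The protocol states no figure to reproduce. The check compares the test schedule with the dosing schedule and then does date arithmetic.

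**Inputs**

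- Pregnancy tests: visit 1 and visit 14 only (section 7.6, flow sheet).
- Injections: visits 8, 9, 10 and 11, taken as days 0, 30, 90 and 180 after the first injection (synopsis, section 4; section 9.4 labels the first as day 1).
- Interval from screening to injection 1, which the protocol gives in three ways:
  - The vaccine preparation chart has visit 2 on day 0 and visit 8 on day 35. Screening is no later than visit 2, so the interval is at least 35 days.
  - Section 9.1 allows at most 60 days.
  - The flow sheet puts screening at month -3, about 90 days.
- Termination visit: month 12, taken as 365 days after injection 1.

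**Age of the last pregnancy test at each injection** = screening-to-injection-1 interval + dosing day

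| Injection | Dosing day | Preparation chart (minimum) | Section 9.1 (maximum) | Flow sheet (approx.) |
|---|---|---|---|---|
| 1 | 0 | 35 | 60 | 90 |
| 2 | 30 | 35 + 30 = 65 | 60 + 30 = 90 | 90 + 30 = 120 |
| 3 | 90 | 35 + 90 = 125 | 60 + 90 = 150 | 90 + 90 = 180 |
| 4 | 180 | 35 + 180 = 215 | 60 + 180 = 240 | 90 + 180 = 270 |

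**Gap between the two scheduled tests**

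- Preparation chart: 35 + 365 = 400 days, about 13 months.
- Section 9.1: 60 + 365 = 425 days, about 14 months.
- Flow sheet: 3 + 12 = 15 months.

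All four injections and the baseline gadolinium scan fall inside this gap on every reading.

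**Is there a test elsewhere?** The visit 8 list (section 9.3) and the month 6 list (section 9.4) have hematology, chemistry and urinalysis only, and the urinalysis panel has no pregnancy test. The flow sheet shows nothing at visits 9, 10, 12 or 13. The number of pregnancy tests after visit 1 and before visit 14 is therefore 0.

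**Where a repeat test could sit before dose 1.** Section 7.4 allows the baseline MRI up to 72 hours before baseline, so with visit 8 on day 35 the earliest scan is on day 35 - 3 = 32. The chart puts visit 7 on day 31, one day before that. A sample taken only at visit 8 could come after the scan.

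**The case against.** Section 7.6 and the flow sheet agree with each other, so this is a deliberate schedule rather than a contradiction. The visit 8 step is a general confirmation of criteria, the flow sheet marks eligibility at visit 1 only, and confirming criteria need not mean repeating every test. That is fair: the point is a judgment that the schedule is too sparse for the rules it serves.

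Eligible women must already use oral contraception or an intra-uterine device. Medical changes are reviewed at visit 8, adverse experiences are reviewed at each injection visit, and the radiologist checks that the patient can undergo MRI. These lower the risk, but none of them is a pregnancy test, and the symptom reviews work only if the woman already suspects. The protocol itself does not rely on contraception alone, since it tests at screening and termination.

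The protocol describes no fetal hazard of the irradiated autologous cells and places no restriction on gadolinium in pregnancy. It also does not say how many of the 30 patients will be women of childbearing potential. All of this stands. The figures above measure the age of a test result; they do not estimate expected exposures.

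The 35-day figure is a lower bound. If visit 2 waits for the seven-day screening proliferation assay in section 9.1, the minimum becomes 35 + 7 = 42 days. The month -3 column conflicts with the 60-day limit. Both points affect the exact age of the result, but the gap remains on every reading. The one-day margin at visit 7 is thin, so the remedy must not depend on it alone.

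**Conclusion.** The concern holds. Followed as written, the protocol permits the first dose on a pregnancy result at least 35 days old and the fourth on one at least 215 days old, with no test between screening and month 12. The ages depend on which of the protocol's three screening intervals is used; the absence of any intermediate test does not.

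It should be fixed as a matter of participant safety. It rests on the protocol's own choice to exclude and withdraw pregnant women, not on a demonstrated fetal hazard. The case is strongest for a repeat test before the baseline MRI and injection 1; tests before injections 2 to 4 follow from the discontinuation rule.

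**What to change.** Amend sections 7.6, 9.3 and 9.4 and the flow sheet as follows.

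1. **Before dose 1:** a serum beta-HCG within a few days before the baseline MRI, with the result known before gadolinium, randomization and injection 1. The visit 7 blood draw serves this when it falls on day 31 as charted; if visit 7 falls earlier, take a separate sample.
2. **Before doses 2 to 4:** a pregnancy test in women of childbearing potential at visits 9, 10 and 11, with the result known before the injection. Visit 11 can use the blood already drawn for the month 6 laboratory tests.

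If only one test is added, choose the first.

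The cost is a few lines of wording, no additional venepuncture at visits 7 and 11, and one inexpensive test at each of visits 9 and 10 for women of childbearing potential only.
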